### Sample size

There is no straightforward, universally accepted method to estimate the required number of participants for developing a multivariable prediction model. Thus, we employed a few alternative methods to estimate the sample size required. We used paternal BMI as an indicator reflective of paternal lifestyle and metabolic factors that are associated with successful pregnancy and expect that it may be retained in the prediction model. Based on the assumption that males with impaired fertility will have an average BMI 1.3 unit higher than the fertile males,^55 56^ and considering a BMI SD of 4 kg/m^2^, a two-sided 5% type 1 error rate and a power of 90%, the minimum required sample size to detect a difference in BMI between cases and controls is 400 couples (200 cases:200 controls). Considering a variance inflation factor of 1.2 for adjustment of maternal factors and other covariates, the study will need to recruit 480 couples (240 cases:240 controls).

Previous studies have reported the use of the event per variable (EPV) ratio:the number of events (success pregnancy) divided by the number of regression coefficients in the model to determine the sample size of a multivariable model.^57^ An EPV of at least 10 has been recommended to avoid overfitting.^58^ We estimate 15 regression coefficients based on the independent male predicting factors of successful pregnancy in the logistic model. Following this guideline, we require 150 events. Given the observed pregnancy rate of 48% in the population,^59^ the total sample size calculated to achieve this number of events is approximately 313 (150/0.48). By accounting for a variance inflation rate of 1.2 for correlation between male and female factors, we will require 376 couples (188 cases:188 controls) in the study.

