We will include the identified male factors from aim 1, along with female factors which are known to be associated with successful pregnancy in a multivariable logistic regression. The male factors will focus on those easily accessible measurements. The female factors include age, BMI, smoking exposure, dietary habit, alcohol consumption and folic acid supplementation, which we have identified in our previous study.^52^ We will also include some important clinical data and other maternal factors such as the duration of active conception attempts, sexual health issues and probable depression in the logistic regression to further select the predictors. To ensure accuracy, we will use weighted logistic regression, adjusting the model based on the updated prevalence of successful pregnancies within a year in the population to correct for sampling biases. The best-fitting model will be determined using Akaike’s information criteria. Subsequently, we will create a point-based scoring system based on the final model coefficients,^53^ making it easily applicable in community settings. Integer points will be assigned depending on the presence or absence of each factor, allowing the estimation of overall probability by summing the points. Higher point values will indicate higher chances of pregnancy. To facilitate calculation of the fertility index score, all continuous variables will be categorised based on clinical thresholds or appropriate percentiles prior to the analysis. We will repeat the same procedures by including male metabolic biomarkers and semen parameters that are associated with successful pregnancy in the weighted logistic regression. This will enable the generation of various versions of the fertility index, catering to different levels of complexity for application in primary and tertiary care settings.

Subsequently, we will use 10-fold cross-validation to assess the performance of the derived logistic regression models and respective fertility index scores. This cross-validation procedure helps evaluate the model’s performance on different subsets of the data, providing an estimate of its predictive ability and generalisation performance. The fertility index will be evaluated for its discriminatory ability in predicting chances of pregnancy based on the area under the receiver operating characteristic curve (AUROC), with value >0.80 indicating that the model exhibits a good discriminatory ability or predictive value.

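### The events-per-variable calculation counts only 15 male coefficients; with the nine named female and couple terms, 376 couples give an EPV of 7.8 and the planned 480 give at most 10.0

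*Protocol article*

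**What the plan says.** The Sample size section of the protocol article gives two calculations. The first, on paternal BMI, sets recruitment at 480 couples (240 cases and 240 controls). The second uses EPV, defined as "the number of events (success pregnancy) divided by the number of regression coefficients in the model to determine the sample size" of a multivariable model. The threshold is stated as "An EPV of at least 10 has been recommended to avoid overfitting". The count of coefficients is then given: "We estimate 15 regression coefficients based on the independent male predicting factors of successful pregnancy in the logistic model". From this, "Following this guideline, we require 150 events". Dividing by a population pregnancy rate of 48% gives about 313 couples, and the final step reads "By accounting for a variance inflation rate of 1.2 for correlation between male and female factors, we will require 376 couples", split 188:188.

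The Statistical analysis plan section, Aim 2, describes the model to be fitted. The male factors from Aim 1 are entered "along with female factors which are known to be associated with successful pregnancy in a multivariable logistic regression". Six female factors are named: age, BMI, smoking exposure, diet, alcohol and folic acid. Three further clinical or maternal factors are given as examples from an open list: duration of trying to conceive, sexual health issues and probable depression. All continuous variables are to be categorised, with the number of categories not stated. Points are assigned by the presence or absence of each factor. Further versions of the index add male metabolic biomarkers and semen parameters.

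**The concern.** The definition of EPV covers every coefficient in the model, but the count covers only the male ones. The model in Aim 2 contains at least nine terms that the calculation leaves out. The only allowance for female factors is the factor of 1.2, described as "By accounting for a variance inflation rate of 1.2 for correlation between male and female factors". An inflation for correlated predictors addresses loss of precision; it does not count the added predictors as coefficients.

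The protocol cites the EPV threshold as its protection against overfitting, and the resulting point score is meant for community, primary and tertiary care. If the rule is met only for part of the model, the stated protection does not apply to the score that would be used.

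**Working it through.** **Inputs.** From Sample size: minimum EPV 10; 15 male coefficients; pregnancy rate 48%; inflation 1.2; EPV-based size 376 couples (188:188); planned recruitment 480 couples (240:240). From Aim 2: six named female factors plus three named clinical or maternal factors, making nine. Events are pregnancies, that is, the control couples.

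**Reproducing the protocol's figure.**
- Events = 10 × 15 = 150.
- Couples = 150 / 0.48 = 312.5, rounded to 313.
- With inflation, 313 × 1.2 = 375.6, rounded to 376.

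The arithmetic is correct for 15 coefficients. What is wrong is the number of coefficients put in.

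**Does the 1.2 factor pay for the omitted terms?** Read as generously as possible, 188 events at EPV 10 support 188 / 10 = 18.8, so 18 whole coefficients. That leaves 18 − 15 = 3 for at least nine terms.

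**EPV with the named terms counted.** At one coefficient each, 15 + 9 = 24.
- At the 376 couples of the EPV calculation: 188 / 24 = 7.8.
- At the 480 couples to be recruited: 240 / 24 = 10.0.

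**Sensitivity at 240 events.** The documents do not give the number of categories or the full list of factors, so the totals beyond 24 are assumptions.

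| Coefficients | EPV at 240 events |
|---|---|
| 24 | 10.0 |
| 25 | 9.6 |
| 30 | 8.0 |
| 36 | 6.7 |

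**The protocol's own chain with 24 coefficients.** Events = 10 × 24 = 240; 240 / 0.48 = 500; 500 × 1.2 = 600 couples. With the 1:1 split in place of 48%: 2 × 240 = 480 couples without the inflation, and 480 × 1.2 = 576 with it. So 480 couples meet the rule for 24 terms only if the 1.2 factor is dropped.

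**The 48% rate.** In a 1:1 case-control design the proportion of events is fixed at 50%. The paragraph itself ends at 188:188, whereas 376 × 0.48 is about 180. The effect is small and conservative: 150 / 0.5 = 300, and 300 × 1.2 = 360, fewer than 376.

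**The case against.** The strongest reply is that the study will not recruit 376 couples. That figure comes from one of several alternative methods; the BMI calculation sets recruitment at 480. At 480 couples, 15 + 9 terms give exactly 10.0. This stands. A reader might infer that the study fails to deliver an EPV of 10, but the nine named factors alone do not show that. The shortfall is unconditional only for the 376-couple figure. At 480 it depends on further terms, on factors with more than two levels, or on keeping the 1.2 inflation.

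A reader might also infer a far lower EPV. Three levels for every factor would make 48 coefficients and 240 / 48 = 5.0. Counting about 38 male items from Table 1 plus nine would give 240 / 47 = 5.1. The documents support neither. Only continuous variables are to be categorised, the number of levels is not given, and presence-or-absence scoring fits one binary term per factor. Table 1 lists data collected, not model terms. The base index is limited to easily obtained male measurements, and biomarkers and semen parameters enter later versions only.

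It can further be said that selection by Akaike's criterion may retain fewer than 24 terms, which would raise the EPV under the protocol's definition. That is possible. Counting every candidate before selection is a stricter standard than the one the protocol states, and this point does not rely on it. Selection does not repair the calculation, though, which assumes 15 male terms and no others. The planned 10-fold cross-validation measures overfitting but does not prevent it.

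**Conclusion.** The EPV calculation is wrong under its own definition: it leaves out at least nine terms that Aim 2 puts in the model. With them, the stated 376 couples give an EPV of 7.8 against a minimum of 10. The planned 480 couples give at most 10.0, with no reserve. One more coefficient, from the open list or from a factor with three levels, brings it to 9.6. The biomarker and semen versions also fall below 10 if they add terms to a full 24-term model, since they bring no new events.

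This rests on 15 male terms being entered as the protocol estimates, on one coefficient for each of the nine named additional factors, and on 240 events from full 1:1 recruitment. It is a defect in the stated justification and in the margin for the model, not evidence that 480 couples are too few.

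**What to change.** Replace the 376-couple calculation with an EPV restated from the 240 events that the 1:1 design fixes, without the 48% population rate. Count all male, female, couple and category coefficients entered in each version of the index, including the versions with biomarkers and semen parameters. For each version, either keep the total at or below 24, or state the lower EPV that results and apply shrinkage to the final coefficients before converting them to points.

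The cost is one rewritten paragraph, and either a shorter predictor list or a less favourable stated EPV. Recruitment of 480 couples need not change.

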### Ethics and dissemination

The study has been approved by the Centralised Institutional Review Board of SingHealth (2024/2120), Singapore. The study will be performed in accordance with the ethical principles in the Declaration of Helsinki. Written informed consent will be obtained from all participants. Findings from this study will be disseminated via peer-reviewed publications, conference presentations and reports to the funding body. The data that support the findings of this study are available from the corresponding author on reasonable request.

## Discussion

In this study, we will comprehensively investigate multiple factors in males, including clinical, biological, behavioural, lifestyle, environmental and molecular characteristics, to understand their relationships with male reproductive health and successful pregnancy. State-of-the-art automated technology integrated with artificial intelligence algorithms will be used to measure sperm DNA fragmentation and assess biofluid oxidative status. This approach will provide crucial insights for reproductive healthcare, defining male fertility status and guiding fertility treatment decisions. Additionally, the assessment of sperm gene expression and DNA methylation will allow understanding of how male exposures affect fertility at a molecular level, aiding in identifying novel candidate biomarkers for predicting the chances of conception and potentially offspring health. These advancements represent a significant step towards implementing an entirely new class of precision medicine in male fertility care, enabling personalised management plans.

Furthermore, the study aligns with the POHaD paradigm, which recognises optimal paternal health as an essential component, along with maternal health, to create a favourable environment that has tremendous potential to influence the birth and growth of healthy children. These efforts will help mitigate the burden of the transgenerational cycle of chronic disease development within families and the wider population. Importantly, the findings of this study will raise awareness among healthcare agencies and the general public about the significant role of men (an essential but often neglected component) and the importance of optimising men’s health during preconception to improve reproductive health outcomes. By focusing on the father’s role in reproductive health outcomes through an evidence-based approach, there is a move to address the disproportionate burden placed on women and promote equity in healthcare and society, in addition to the growing evidence of the influence of sperm quality on reproductive outcomes.

Several limitations exist within this study. First, self-reported dietary and lifestyle information may be subjected to recall bias, potentially compromising the predictive accuracy of successful pregnancy. Individuals may provide biased estimates of self-assessed behaviour due to various factors, including misunderstanding or social desirability. While these types of bias are inherent to some extent, we endeavour to minimise them by using standardised and well-structured questionnaires and by avoiding long recall periods as much as possible. Second, given the study’s observational design, any causal link between risk factors and male subfertility remains inferential, with the potential for residual confounding. To address this limitation, we will use propensity score methods and conduct sensitivity analyses, including interaction testing and stratification by key confounders, to enhance the robustness of our findings. Additionally, our recruitment is exclusive to Singapore residents, potentially limiting the broader applicability of our results to other contexts. However, given the multiracial population of Chinese, Malay and Indian, the results obtained are likely generalisable to Asians.
